##### Quality of life

The WHOQoL-BREF will be used to measure quality of life. The WHOQoL-BREF consists of 24 items divided into the domains physical health, psychological, social relationships, and environment and two general health items. [43].

##### Cardiorespiratory fitness

Cardiorespiratory fitness will be measured with a VO_2_ max assessment with the Åstrand Bike Test. The submaximal Åstrand Bike Test is considered a low invasive VO_2_ max test because of its duration of 6 min and people do not need to perform at maximum capacity [44, 45].

##### Postural adjustment and movement sequencing in gait

A real-time video camera and markerless motion capture camera’s is set up to measure postural adjustments and movement sequencing in gait. The technological application of markerless motion capture during the gait analysis supports the validation in calculating body proportions (angles between body parts), timing, direction, and velocity without attaching markers to the skin. The main items of observation are; Posture, movement initiation and movement sequencing [46–49].

##### Movement disturbances

The Sint Hans Rating Scale will be also used to measure movement disturbances. The Sint Hans Rating Scale is an evaluation tool for akathisia, dyskinesia, dystonia, and Parkinsonism. It consists of 29 items divided into four dimensions of movement disturbances [50].

##### Cardiometabolic disease risk factors

Blood pressure, waist circumference, and BMI are measured during the measurement in the UMCU. The Dutch guideline on somatic screening for people with SMI recommends doing a yearly somatic screening including a blood test to test HbA1c, total cholesterol, LDL-cholesterol, HDL-cholesterol, and triglycerides. The results of this blood test will be retrieved from the psychiatrist or general practitioner when patients give permission.

Attendance at intervention group activities will be monitored.

### Mental health worker

#### Primary outcome

##### Physical activity and lifestyle habits

The primary outcome for the mental health worker is their physical activity and lifestyle habits. The IPAQ-SF and the Dutch Healthy Diet Index will be conducted. The Dutch Healthy Diet Index is a screener for dietary quality based on Dutch and international nutrition guidelines and assesses 15 components of the Dutch dietary guidelines [51]. They will also be asked for their smoking status, drinking habits, length, and weight.

#### Secondary outcome

##### Personality traits

The personality traits will be measured with the NEO five-factor inventory. The NEO five-factor inventory is a 60-item questionnaire that measures the five domains of personality neuroticism, extraversion, openness, agreeableness, and conscientiousness [52].

#### Implementation barriers and facilitators

At the end of the intervention period, we will conduct semi-structured interviews on the implementation of the intervention with the location managers and dedicated mental health workers. Questions on the content of the intervention, barriers and facilitators during the implementation process, and perceived outcomes of the intervention will be asked. Interviews will be recorded, transcribed, and analyzed by direct content analysis by two researchers independently. We will also evaluate the implementation by monitoring which sports activities are provided, what the frequency of the lifestyle courses is and we will assess the percentage of patients in which physical activity goals are part of the guidance plan.

### Measurements

Table 1 provides an overview of the scheduling of the measurements and Table 3 shows the content of the measurements. The online questionnaire always consists of the SFS. To lower the burden on patients and to increase the reliability of the answers we will include the WHOQOL-BREF or the BSI in the online questionnaire in alternating order. This order will be decided based on randomization. The mental health worker will receive one online questionnaire.

**Table 3 Tab3:** Overview of measurements

**Patient**	
**Baseline measurement (T = 0)**	Sex, age, diagnosis, form of supported housing, smoking and drinking habits **Questionnaires**: SFS, BSI/WHOQOL-BREF
**Measurements at the UMCU (In the intervention groups: prior to the start of intervention and 12 months after the start of intervention)**	Medication use, smoking, and drinking habits **Questionnaires**: SFS, BSI, WHOQoL-BREF, IPAQ-SF, Sint Hans Rating Scale, structured questionnaire to indicate physical complaints that may influence gait, structured medication questionnaire **Measurements**: VO_2_ max Åstrand Bike test (submaximal), posture and gait analysis with a real-time video camera and markerless motion capture, blood pressure, length, weight, waist circumference Blood tests retrieved from medical records: HbA1c, total cholesterol, LDL-cholesterol, HDL-cholesterol, triglycerides
**Online questionnaire measurement (T = 3, 6, 9, 12, 15, 18, 21)**	**Questionnaires**: SFS, BSI/WHOQOL-BREF
**Mental health worker**	
**Baseline measurement (T = 0)**	Sex, age, length, weight, smoking and drinking habits **Questionnaires**: IPAQ-SF, Dutch Healthy Diet Index, NEO five-factor inventory

### Research procedures

This study will be conducted according to the principles of the Declaration of Helsinki (amended version in October 2013) and following Good Clinical Practice guidelines from the European Medicines Agency (ICH E6, R2) and the Medical Research Involving Human Subjects Act (WMO).

### Recruitment

Patients will be recruited via their key mental health worker. Mental health workers will receive instructions and flyers about the study. During the recruitment phase and baseline measurement patients will not get detailed information on the elements of the Muva intervention, but are broadly informed that the study is about examining and improving the mental and physical health of people with SMI. This is done to limit selection bias since patients that are interested in physical activity might be more likely to participate in a study on increasing psychical activity. After the patient agrees to participate, the patient’s key mental health worker will also be recruited. Patients will receive two vouchers of in total of 50 euros for their participation to reimburse time and travel costs.

### Statistical analyses

#### Sample size

The sample size is calculated for the primary outcome social functioning. For the SFS we assumed an intra-cluster correlation of 0.1, a between-level correlation of 0.8, and a standard deviation of 9 [34, 41]. The anticipated dropout rate is 30%, as physical activity interventions in mental health care have average dropout rates of 26.7% [19]. We performed simulations to determine the power of the trial design to demonstrate an increase of at least 3 points after one year in the SFS. With measurements on seven time points in 100 patients, the study will have a power of 0.93.

### Data analysis

The primary analysis in this study evaluates if the Muva intervention improves social functioning in comparison to care as usual. This will be analyzed with a mixed-effects linear regression model taking into account clustering of outcome measurements within individuals and centers using random effects and possible confounding factors age, gender and diagnostic subgroups using fixed effects. In addition, we will include lifestyle habits and character traits of the mental health worker as dependent variables to analyze the association between the mental health workers’ characteristics and the outcome social functioning.

Modified intention-to-treat analysis will be done, but if patients move to a team of the supported housing organization without the Muva intervention or rehabilitation care stops within 3 months of intervention, patients will be analyzed in the control group since they will no longer receive the Muva intervention. Patients that drop out from the study, will be analyzed in the group they participated in.

Sensitivity analysis will be performed on cluster, attendance at intervention activities, and medication changes. Dropout analysis will be performed. Analysis will be done in IBM SPSS statistics 25 and R version 4.0.4, using a 95% confidence interval (*p* < 0.05).

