## Objectives

We designed the Muva physical activity intervention for people with SMI to improve their social functioning. The intervention focuses on increasing physical activity by implementing group sports activities, active weekly meetings with mental health workers, and a serious game to set physical activity goals. The intervention aims to decrease barriers to physical activity through active involvement of the mental health worker, supporting lifestyle courses, and a medication review.

We will investigate if social functioning and mental and physical health of patients can improve through this package of interventions. We hypothesize that social functioning and quality of life will improve, psychiatric symptoms will decrease, and physical health will improve with an increase in cardiorespiratory fitness, and a decrease in movement disturbances and cardiometabolic disease risk factors.

To gain understanding on movement disturbance severity and the impact on motor execution in SMI, the Sint Hans Rating Scale and gait analysis with markerless motion capture will be performed during the physical measurements in the UMCU. The obtained results may provide new information on which specific movement interventions are recommendable for a better and sustainable implementation of physical activities for people with SMI in the future.

Moreover, we will examine if the lifestyle habits and/or personality type of the mental health worker are associated with the outcomes. Our hypothesis is that mental health workers with healthier lifestyles and a conscious personality type can contribute more to an active and healthy lifestyle of their patients since they might value physical activity as important and are able to consciously plan physical activities and oversee barriers for patients. In addition, we aim to evaluate the barriers and facilitators of the implementation of the intervention by conducting semi-structured interviews with location managers and mental health workers.

This paper aims to describe the Muva study in detail according to the SPIRIT statement [39].

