### Methods

#### Study design and setting

This study is a pragmatic stepped wedge cluster randomized controlled trial that will be conducted at supported housing organization Lister and the University Medical Centre Utrecht (UMCU) in the Netherlands. This design allows us to implement the intervention sequentially in the participating teams and to study the effects of the Muva intervention.

A supported housing organization is an organization that supports people with SMI in their rehabilitation by giving assistance in several domains in patients’ lives such as housing, daily activities, (voluntary) work, building a social network and finances in order to promote independency. Within this setting, they do not provide psychiatric treatment, this is provided by the general practitioner or a psychiatrist from another organization. Patients have a key mental health worker, with a mental health degree of a university in applied sciences, who is responsible for the guidance plan and the rehabilitation support. This worker has guidance meetings with the patient for at least once a week, but more frequently if the condition of the patient requires more support. The patient population of Lister is diverse with patients living independently and receiving ambulatory care, patients who live in small assisted living facilitations and patients who live in a (group) house with 24 h care.

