All teams of the supported housing organization (*n* = 30) will be invited to participate in the study. Teams in four different areas of Utrecht will be chosen to participate to prevent spillover effects and contamination since teams work closely together in these areas. Every area will form a cluster. Three clusters will start the intervention in a stepped wedged order, within intervals of three months, and one cluster will remain the control group during the study period (Table 1). To determine which area is allocated to which cluster to start the intervention, a simple randomization method is performed by drawing lots. Hence, randomization is done at cluster level and not at patient level. Randomization at patient level is not possible since teams deliver equal rehabilitation care to the patients of their team. Given the stepped wedge design and the vulnerable patient group, for whom continuity of research team is desired, participants and the research team know when each cluster will crossover from unexposed to the exposed period, also reducing the possibility of drop-out. Nevertheless, to reduce rater bias the final measurement at the 21th month of the study, will be performed blind to the intervention exposure duration (Table 1).

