### Study population

We will recruit 100 patients and their mental health workers. All participants will be informed about the study and asked for consent. Patients are included if they are ≥ 16 years old, diagnosed with a severe mental illness (i.e., a psychiatric disorder classified by the DSM-5 causing serious limitations in psychosocial functioning for a duration of ≥ 2 years), and can give informed consent and read and speak Dutch. Patients are not eligible for inclusion if their psychiatric condition hinders informed consent or/and participation in the intervention according to their mental health workers.

Mental health workers are included when they can give informed consent and read and speak Dutch.

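### The worker-trait analysis names no key-worker level, so its standard errors are too small if study patients share key workers and those workers differ beyond the measured traits

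*Protocol article*

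**What the plan says.** All references are to the protocol article.

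- **Data analysis** sets up the primary analysis as a mixed-effects linear regression "taking into account clustering of outcome measurements within individuals and centers using random effects", with age, gender and diagnostic subgroup as fixed effects. It continues: "we will include lifestyle habits and character traits of the mental health worker as dependent variables to analyze the association". The purpose given is "to analyze the association between the mental health workers’ characteristics and the outcome social functioning". No worker level is named, and the random effects are not restated for this second analysis.
- **Objectives** poses the question: "we will examine if the lifestyle habits and/or personality type of the mental health worker are associated with the outcomes". The accompanying hypothesis names two features, a healthier lifestyle and a conscientious personality.
- **Study design and setting** says "Patients have a key mental health worker, with a mental health degree of a university in applied sciences", and on the randomized units, "Every area will form a cluster"; there are four.
- **Recruitment** says that patients are approached through their key worker, and then: "After the patient agrees to participate, the patient’s key mental health worker will also be recruited".
- **Study population** gives the size: "We will recruit 100 patients and their mental health workers". It gives no number of workers.
- **Table 3** shows one worker questionnaire, at baseline, containing the IPAQ-SF, the diet index, smoking, drinking, length and weight, and the NEO inventory.

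**The concern.** A trait measured once on the worker is a worker-level covariate. All study patients of that worker carry the same value, so the unit that supplies information about the trait is the worker, not the patient. A patient intercept handles repeated SFS scores within a person, and a center intercept handles similarity within a center. Neither represents two patients in the same center being alike because they have the same worker. Without a worker term, the model treats them as independent replicates of the trait comparison.

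Workers may differ in ways the questionnaires do not capture, such as skill, caseload mix or the house they work in. Part of that variation will then line up by chance with whichever trait is tested, and the standard error will not allow for it. The role of the worker is a stated objective and one of the contributions promised in the Discussion, so a trait association with too narrow an interval could be reported as a finding. The Background and Discussion also argue that workers matter to patients' progress, which makes zero residual variation between workers an uncomfortable assumption.

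**Working it through.** **The plan's own figure.** The only power figure is 0.93, for the intervention effect on the SFS (Sample size section). It concerns the randomized comparison. It depends on simulation details and a table that are not shown, so it could be neither confirmed nor refuted, and it has no bearing here. The article gives no figure for the worker-trait analysis.

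**Inputs from the article.** 100 patients; 4 areas; intra-cluster correlation 0.1; between-level correlation 0.8, read here as the within-person correlation over time; SD 9, so total variance 81; 7 time points; p < 0.05, taken as two-sided.

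**Inputs assumed, because the article does not give them.** Patients per worker m = 1, 2, 4 or 5, that is 100, 50, 25 or 20 workers with equal caseloads. Worker share of total SFS variance w = 0, 0.05, 0.10 or 0.20.

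**Step 1: variance of a patient's mean within a center, as a share of 81.** The center takes 0.1, leaving 0.9. Of this, 0.8 × 0.9 = 0.72 is stable over time (worker plus patient). The remaining 0.2 × 0.9 = 0.18 is occasion-level and is averaged over 7 time points:

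0.72 + 0.18/7 = 0.7457.

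**Step 2: correlation between two patients of one worker, given center.** ρ = w / 0.7457, which is 0.067, 0.134 and 0.268 for w = 0.05, 0.10 and 0.20.

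**Step 3: design effect for a worker-level covariate.** DE = 1 + (m − 1)ρ. The standard error that ignores workers is too small by a factor of about √DE. A rough false-positive rate is therefore 2[1 − Φ(1.96/√DE)].

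**Step 4: simulation check.** 2000 runs per cell, one trait with no true association, REML on patient means with a random center. The comparison analysis adds a worker level by analysing worker means, which is equivalent when caseloads are equal. The Monte Carlo standard error near 5% is √(0.05 × 0.95/2000) = 0.005.

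| m | w | DE | Approx. rate | Simulated, no worker level | Simulated, worker level |
|---|---|---|---|---|---|
| 2 | 0.05 | 1.07 | 0.058 | 0.058 | 0.053 |
| 2 | 0.10 | 1.13 | 0.066 | 0.072 | 0.057 |
| 2 | 0.20 | 1.27 | 0.082 | 0.083 | 0.049 |
| 4 | 0.05 | 1.20 | 0.074 | 0.087 | 0.061 |
| 4 | 0.10 | 1.40 | 0.098 | 0.119 | 0.062 |
| 4 | 0.20 | 1.80 | 0.145 | 0.162 | 0.059 |
| 5 | 0.05 | 1.27 | 0.082 | 0.095 | 0.060 |
| 5 | 0.10 | 1.54 | 0.114 | 0.125 | 0.063 |
| 5 | 0.20 | 2.07 | 0.173 | 0.182 | 0.061 |

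With m = 1, both analyses give 0.051 to 0.056 at every w. With w = 0 and m above 1, the analysis without a worker level gives 0.052 to 0.062. So both conditions, shared workers and residual worker variance, are needed for material inflation. With a worker level, every cell lies between 0.049 and 0.064.

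A separate simulation with unequal caseloads and w = 0.10 gave single-trait rates of 0.073 (50 workers), 0.085 (40), 0.096 (33) and 0.109 (25), which agrees.

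**The case against.** The strongest reply is that the premise is not in the document. Nowhere does the article say that study patients share key workers, and with one patient per worker nothing is wrong. The size of residual worker variance is likewise unstated. This stands, and it is why the conclusion is conditional. Sharing is still plausible, because patients are recruited through their key worker and one worker can bring in several.

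Second, the sentence with the random effects describes the primary comparison, and details of a secondary analysis often sit in an analysis plan that is not shown. This stands in part. The article does not exclude a worker level. But it does fix a structure and then adds the traits to it, so a reader would take the named effects as the model.

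Third, a reader might infer stronger things, which the documents do not support:

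- *That chance differences between workers will be declared trait associations.* Even in the worst cell above, about 82% of single-trait tests do not reject.
- *That a false claim about some trait is more likely than not.* With ten unadjusted tests and w = 0.10, simulated any-of-ten rates were 48 to 60%. Most of that is multiplicity: the rate is already 36 to 40% with no worker variance or with one patient per worker. The article does not specify ten separate tests.
- *That a joint test of all traits is badly inflated.* No joint test is planned.
- *That the article contradicts itself by assuming no worker variance.* It argues that workers' support, lifestyle and conscientiousness matter, and the latter two are among the modelled terms. It does not assert large variation beyond the measured traits.
- *That the intervention effect is compromised.* Nothing here shows that.

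**Conclusion.** The point holds in conditional form. Read naturally, the worker-trait analysis uses random effects for patients and centers only, while its covariates vary only between workers. If key workers are shared and differ beyond the measured traits, the single-trait type I error is about 6 to 8% at 2 patients per worker, 9 to 16% at 4 and 10 to 18% at 5. The worker shares of 5 to 20% and the caseloads behind these figures are assumptions. The result also rests on equal caseloads and on the stated 0.8 being a within-person correlation.

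This is a non-randomized association analysis, so the point is worth correcting but does not touch the trial's main conclusion. The same sentence needs a wording repair regardless: it labels the traits as dependent although social functioning is the outcome, and the calculations here treat them as explanatory.

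**What to change.** For the worker-characteristics analysis:

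1. Add a random intercept for key mental health worker, with patients nested in workers and workers within centers.
2. Test worker-level terms with degrees of freedom that reflect the number of workers (Satterthwaite or Kenward-Roger).
3. Call the lifestyle habits and traits explanatory variables.
4. State the expected number of workers and of patients per worker, so that readers can judge how much the worker level matters.

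The cost is a few lines of analysis text. The patient-worker link should already be available, because each patient's key worker is recruited. No extra data or patients are needed. The downside is wider intervals for worker traits and fewer nominally significant ones.

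Separately and optionally: many traits are available at p < 0.05 and the article gives no multiplicity rule. Traits other than the healthier lifestyle and conscientiousness hypothesized under Objectives are best reported as exploratory.

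### The primary model names no area-by-period variation although four areas are randomised; if areas drift differently over 21 months, the 5% test rejects too often

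*Protocol article*

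**What the plan says.** Under Study design and setting, the protocol article makes the area the randomised unit: "Every area will form a cluster", and "randomization is done at cluster level and not at patient level". There are four areas: "Three clusters will start the intervention in a stepped wedged order, within intervals of three months, and one cluster will remain the control group". Lots decide which area takes which position.

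Under Data analysis, the primary comparison is a mixed-effects linear regression "taking into account clustering of outcome measurements within individuals and centers using random effects". The fixed part lists "possible confounding factors age, gender and diagnostic subgroups using fixed effects". The test is at p < 0.05 with a 95% interval. The word 'centers' is not defined; elsewhere the article speaks of areas, clusters, teams and locations. A sensitivity analysis on cluster is announced without detail.

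Under Sample size, the planning values are "an intra-cluster correlation of 0.1, a between-level correlation of 0.8, and a standard deviation of 9", with 30% dropout, 100 patients, seven time points and a power of 0.93 for 3 points on the Social Functioning Scale. The article does not say which correlation the 0.8 is.

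**The concern.** Exposure is the same for everyone in an area at a given time. The treatment effect is therefore estimated from how the area means move relative to one another. A person effect and a constant area effect remove stable differences, and period effects remove movement common to all areas. Neither removes movement peculiar to one area between two occasions. If that movement exists and the model has no term for it, it enters the treatment estimate but barely enters its standard error. With four areas there is little to average it out.

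At stake is the error rate of the primary test: a significant result could reflect ordinary drift among four areas. The undefined 0.8 adds to the difficulty, because the reader cannot tell whether planning allowed for drift.

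**Working it through.** **The plan's own figure.** Power was computed as Φ(3/SE − 1.96), with SE from generalised least squares for a closed cohort in four areas, period effects, total variance 9² = 81 and intra-cluster correlation 0.1.

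- With 0.8 read as a person-level correlation, no area-by-period variance and an effect growing linearly to 3 points at 12 months, power is 0.915 (visits at months 0 to 18, starts after months 0, 3 and 6, gradual 30% dropout). It is 0.916 to 0.940 with seven visits, starts after months 3, 6 and 9 and no dropout. The stated 0.93 is reproduced to within 2 points.
- This is not the only match. An immediate effect with an area correlation across periods of 0.90 gives 0.916 to 0.935 with seven visits.
- With an area correlation of 0.80, no variant tried exceeds 0.86.

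**Inputs for the error rate.** From the protocol: four areas, SD 9, intra-cluster correlation 0.1, 100/4 = 25 patients per area (100 × 0.7/4 = 17.5 with 30% dropout), and eight occasions (month 0 and every three months to 21, Table 3). Assumed: person-level correlation r of 0.8 or 0.5 within an area; area correlation across periods c of 1.0, 0.95, 0.90 or 0.80; area-by-period effects independent of each other; period effects in the model.

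**Formulas.**

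- Within-person residual variance: e = 81 × 0.9 × (1 − r). For r = 0.8 this is 14.58; for r = 0.5 it is 36.45.
- Area-by-period variance: d = 81 × 0.1 × (1 − c). This is 0.405, 0.81 and 1.62 at c = 0.95, 0.90 and 0.80. At 0.95 the standard deviation is √0.405 = 0.64 points, against a target of 3.
- With m patients per area, the model without the term takes the variance of an area-period mean, beyond area and period effects, as e/m. The true value is e/m + d. The design constant cancels, so the start months do not matter here.
- Rejection rate under no effect = 2 × [1 − Φ(1.96 × √{(e/m)/(e/m + d)})].

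**Numbers for r = 0.8, m = 25 (e/m = 0.583).**

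- c = 0.95: √(0.583/0.988) = 0.768; 1.96 × 0.768 = 1.51; rate 13.2%.
- c = 0.90: √(0.583/1.393) = 0.647; 1.96 × 0.647 = 1.27; rate 20.5%.
- c = 0.80: √(0.583/2.203) = 0.514; 1.96 × 0.514 = 1.01; rate 31.3%.

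In practice the fitted residual variance absorbs a little of the drift. For 100 patients it becomes e + m × d × 20/692, where 20 is the area-by-period degrees of freedom (3 × 7 − 1) and 692 = 800 − 100 − 8 the residual ones. For 70 patients the 692 becomes 560 − 70 − 8 = 482. This lowers each rate slightly.

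| Setting | c = 1.0 | 0.95 | 0.90 | 0.80 |
|---|---|---|---|---|
| r = 0.8, m = 25, formula | 5.0% | 13.2% | 20.5% | 31.3% |
| same, residual adjusted | 5.0% | 12.8% | 19.6% | 29.5% |
| same, simulated (1,500 trials each, REML) | 5.5% | 13.9% | 20.3% | 31.4% |
| r = 0.8, m = 17.5, formula | 5.0% | 10.8% | 16.3% | 25.3% |
| same, residual adjusted | 5.0% | 10.4% | 15.5% | 23.5% |
| r = 0.5, m = 25, formula | 5.0% | 8.3% | 11.6% | 17.7% |
| same, residual adjusted | 5.0% | 8.2% | 11.3% | 17.1% |

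Reading 'centers' as teams changes little: with five teams per area (assumed), the rates are 13.1%, 19.4% and 28.5%.

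**With drift allowed for.** An analysis of area-period means with area and period fixed and t on 20 degrees of freedom (eight visits, 25 per area, r = 0.8, starts after months 3, 6 and 9, immediate effect) has 95% half-widths of 1.41, 1.68 and 2.11 points at c = 0.95, 0.90 and 0.80. Ignoring the drift gives about 1.02. Power for 3 points is 0.99, 0.94 and 0.81; with linear growth to 3 points at 12 months it is 0.85, 0.72 and 0.52.

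**The case against.** The article condenses a fuller protocol, and a statistical analysis plan may exist. Degrees-of-freedom methods and extra variance terms are often left to those. The text says random effects, not random intercepts only, so a richer structure is not excluded. All this stands as a limit on the claim. Still, the article does state the clustering levels of its primary model, and area-by-period is not among them. The announced sensitivity analysis on cluster would not change the primary test.

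A reader might infer that the interval is too narrow as a matter of fact. The document does not support that, because it gives no area-by-period variance and with none the test holds 5%. All areas belong to one organisation and share one lifestyle campaign, so much of the movement over time may be common to them, and period effects would absorb it. Uneven implementation is no argument either: if the intervention has no effect, delivering it unevenly does not move area means.

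A reader might also infer that the sample size assumed drift which the analysis then drops. That needs the 0.8 to be an area's correlation across periods, a reading that fits the stated power poorly (at most 0.86 against 0.93). The top of the 13% to 30% range also uses 0.8 twice, for persons and for areas.

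**Conclusion.** The point holds conditionally. For a design with four randomised areas, the primary model as described has no named term for the variation that decides its standard error, and its 'centers' cannot be tied to the randomised unit.

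If the area correlation across periods is between 0.95 and 0.80, the nominal 5% test rejects about 13% to 30% of the time under no effect (25 per area, person-level correlation 0.8, period effects included). That becomes about 10% to 25% after 30% dropout and about 8% to 17% with a person-level correlation of 0.5. With no area-by-period variation it is 5%. The correlations across periods are assumptions, not figures from the protocol. Little drift is needed, however: the 0.95 case is a standard deviation of 0.64 points.

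**What to change.** Before analysis:

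1. Define 'centers' as the four randomised areas.
2. State what the between-level correlation of 0.8 is: within a person, or within an area across periods.
3. Add an area-by-period random effect to the primary model, with period effects in the fixed part, and use Kenward-Roger or Satterthwaite degrees of freedom.
4. Restate the power under that model, over a range of area correlations.

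A permutation p-value over the 4! = 24 possible lot drawings is an optional check only. Its smallest attainable value is 1/24 = 0.042, so it can reject only when the realised order is the most extreme of all.

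The cost is a few lines of R, which is already planned software, and no new data. The interval widens (in the example above, from about 1.02 to between 1.41 and 2.11 points either side) and the stated power becomes less favourable. The repair is not perfect. In simulation the added term brought a rate of about 29% down to 7% to 9% with a normal reference and to about 7% with t on 20 degrees of freedom. The Kenward-Roger and Satterthwaite versions were not simulated.
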